## Abstract

**Background:**

Patients with multimorbidity and complex health needs are defined as a priority by the World Health Organization (WHO) and the European Union. There is a need to develop appropriate strategies with effective measures to meet the challenge of chronicity, reorienting national health systems. The increasing expansion of mobile health (mHealth) interventions in patient communication, the reduction of health inequalities, improved access to health care resources, adherence to treatment, and self-care of chronic diseases all point to an optimistic outlook. However, only few mobile apps demonstrate their effectiveness in these patients, which is diminished when they are not based on evidence, or when they are not designed by and for users with different levels of health literacy (HL).

**Objective:**

This study aims to evaluate the efficacy of an mHealth intervention relative to routine clinical practice in improving HL and self-management in patients with multimorbidity with heart failure (HF) and complex health needs.

**Methods:**

This is a randomized, multicenter, blinded clinical trial evaluating 2 groups, namely, a control group (standard clinical practice) and an intervention group (standard clinical practice and an ad hoc designed mHealth intervention previously developed), for 12 months.

**Results:**

The contents of the mHealth intervention will address user-perceived needs based on the development of user stories regarding diet, physical exercise, cardiac rehabilitation, therapeutic adherence, warning signs and symptoms, and emotional management. These contents have been validated by expert consensus. The creation and development of the contents of the mHealth intervention (app) took 18 months and was completed during 2021. The mobile app is expected to be developed by the end of 2022, after which it will be applied to the experimental group as an adjunct to standard clinical care during 12 months.

**Conclusions:**

The trial will demonstrate whether the mobile app improves HL and self-management in patients with HF and complex health needs, improves therapeutic adherence, and reduces hospital admissions. This study can serve as a starting point for developing other mHealth tools in other pathologies and for their generalization to other contexts.

**Trial Registration:**

ClinicalTrials.gov NCT04725526; https://tinyurl.com/bd8va27w

**International Registered Report Identifier (IRRID):**

DERR1-10.2196/35945

## Introduction

### Care of Patients With Multimorbidity and Heart Failure

Although increased life expectancy, socioeconomic improvements, and biomedical innovations have led to a reduction in mortality, they have also led to a considerable increase in chronic conditions. A prevalent paradigm of these socio-health phenomena is the multimorbidity of patients, which is one of the leading health problems of the 21st century. Multimorbidity can alter health outcomes and lead to disability that is more significant or can lead to worse quality of life or frailty [1].

Heart failure (HF) has a high and increasing prevalence and incidence, and is one of the leading causes of morbidity and mortality in the Western world [2]. Further, if we add to this the significant impact of chronic diseases, mainly cardiovascular diseases, cancer, diabetes, and chronic lung diseases [3], the situation becomes even more complicated by the fact that patients are responsible for most of the avoidable hospital admissions. In this line, both the World Health Organization (WHO) and the European Union define a patient with chronic disease as a priority and point out the need to develop appropriate strategies with effective measures to meet the challenge of chronicity, reorienting national health systems [4,5].

According to the latest data published by the WHO [4], heart disease continues to be the leading cause of mortality worldwide. Globally, it was estimated that in 2019, 197.2 million people were living with ischemic heart disease (IHD), and it was more prevalent in males than in females (113.7 and 83.6 million people, respectively). North Africa and the Middle East, Central Asia, and Eastern Europe had the highest prevalence rates of IHD in the world. The number of deaths due to heart disease has increased since 2000 by more than 2 million people, from 6-7 million to almost 9 million people, representing 16% of all deaths. In 2019, IHD mortality rates were 118.0 per 100,000. IHD mortality rates were highest in parts of North Africa and the Middle East, Eastern Europe, and Central Asia [6,7].

In Spain, HF remains an enormous health challenge (estimates suggest that there are more than 1,300,000 people with HF). Besides, more than 17,000 people die from this disease every year, making it the fourth leading cause of death [8] and the third leading cause of cardiovascular death after IHD and cerebrovascular disease. It is also the leading cause of hospitalization in people over 65 years of age; furthermore, 50% die within 5 years of diagnosis. The prevalence of HF increases progressively with age, reaching prevalence rates of 1%, 10%, and 17.4% in the population over 40, 70, and 85 years of age, respectively. There are more than 80,000 admissions per year in Spain for HF, and half of the hospitalized patients are readmitted within 1 year due to decompensation. Likewise, the use of pharmacological and nonpharmacological resources (resynchronizers or defibrillators) in people with HF is growing exponentially [9].

Although there is a growing interest in patients with comorbidity and multimorbidity, from an evidence perspective, this population has been excluded from most clinical trials and intervention studies [10,11]. Interdisciplinary teams based on the collaboration of different care settings and sustainable interventions adjusted to the public system are recommended. Similarly, a model centered on the patient’s needs is reinforced, based on primary care and shared action with hospital care, with proactive and planned interventions aimed at promotion and prevention [12].

### Health Literacy as a Health Asset in Patients With Multimorbidity

In the field of public health and health promotion, health literacy (HL) is presented as a means that allows individuals to exercise significant control over their health and over the personal, social, and environmental determinants that determine it, being considered as an individual asset to be built.

Following the theoretical framework proposed by the European Health Literacy Project (European Health Literacy Survey [HLS-EU]) [13], HL is determined by the combination of the 3 dimensions of health (being sick/health care; being at risk/disease prevention, and being healthy/health promotion) and the 4 ways of managing information (finding it, understanding it, evaluating it, and applying it to one’s own life to make informed decisions). *Access* refers to the ability to seek, find, and obtain health information; *understanding* refers to the individual’s ability to understand the info accessed; *evaluation* describes the ability to interpret, filter, judge, and assess the health information accessed and understood; and *application* refers to the ability to communicate and use the information to decide to maintain and improve health.

Populations that are more likely to experience difficulties in self-managing their diseases are those with low levels of HL [14]. Having poor HL is an independent risk factor for poorer health [15] because of medication errors and a poorer understanding of disease and treatments [16]. Similarly, there is evidence of a relationship between low HL and higher rates of hospital admissions, poorer therapeutic adherence on care plans, and poor use of preventive services [17,18]. In the particular case of people with chronic diseases, HL plays a crucial role in the self-management of their disease [19].

### mHealth: A Digital Health Literacy Proposal

In the last few years, mobile health (mHealth) has emerged prominently as a result of the tremendous sociological and cultural impact of smartphones and tablets.

The Global Observatory for eHealth defines it as “medical and public health practice carried out with the support of mobile devices such as phones, personal digital assistants, Tablets and other wireless communication devices to carry out public health activities and assist in clinical practice” [20].

Despite its expansion in recent years, few studies demonstrate the effectiveness and utility of mHealth in chronic disease self-management beyond diabetes [21,22]. A recent systematic review of clinical trials involving mHealth interventions to improve self-management of patients with chronic diseases, including patients with cancer, HF, fibromyalgia, asthma, and spine bifida, achieved statistically significant effects on health outcomes after the incorporation of mobile apps in disease management [23]. Existing evidence promises an optimistic horizon regarding their effectiveness in chronic diseases [23,24] and, in particular, in patients with cardiac diseases [25,26]. Despite this, we still find contradictory results. For example, the study by Hägglund et al [27] in patients with HF revealed improvements in self-care and quality of life and a reduction in the number of hospitalization days. By contrast, the study by Vuorinen et al [28] found no difference in the number of hospitalization days.

At present, there is a severe deficiency of mHealth tools, which are developed in collaboration with target patients and multidisciplinary teams, are incorporated into daily care practice, and have proven their efficacy in clinical trials [29,30], to improve the self-management of patients with HF having complex health problems. Systematic reviews recently published on this topic [23,25,26] reflect the scarcity of studies aimed at patients with multimorbidity.

Therefore, we aim to develop an app based on the needs of users and deficiencies identified by professionals, which motivates behavior change through gamification strategies, as per scientific evidence and adapted to the user’s level of HL, and to test its effectiveness in terms of self-management and improvement of personal autonomy to perform basic activities of daily living, reduce hospital admissions, promote therapeutic adherence, and increase HL.

## Methods

### Study Design

A randomized, controlled, multicenter clinical trial evaluated the efficacy of an mHealth intervention with 2 groups: a control group (standard clinical practice) and an experimental group (standard clinical practice together with an ad hoc designed mHealth intervention).

### Patient Selection

#### Setting

A total of 4 basic health areas located in the south of Spain, including 2 hospitals, will participate. The health care centers belonging to the clinical management units with the best mortality rates during hospital admission and at 30 days after discharge (12.7% and 14.3 %, respectively) and those with the highest rates (28% and 30.4%, respectively) were considered.

#### Participants

Patients with multimorbidity with HF and complex health need to be attended by the nurse case manager of the primary care or hospital care centers, nurse or family doctor, or specialized care nurse, or area specialist physician of the study area.

#### Diagnostic Criteria

Patients with multimorbidity and HF and complex health needs who meet the following diagnostic criteria [12] will be considered:

Be classified in clinical category A of chronic pathologies for HF that, in a situation of clinical stability, has been in grade II of the New York Heart Association (NYHA) [31], being able to be simultaneously classified, or not, in other clinical categories for having another chronic disease(s) included in these categories.Patients with at least one of the following complexity criteria [12]: extreme polypharmacy (≥10 chronically prescribed active ingredients); sociofamilial risk (Gijon scale score [32] >10 points); pressure ulcers of stage II or higher; malnutrition (body mass index <18.5 kg/m^2^); nasogastric feeding (≥3 months); 2 or more hospital admissions in the previous 12 months.

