#### Description of the Intervention

The mHealth app aimed at empowering HL and self-management of the patients with multimorbidity with HF and complex health needs. It will be developed ad hoc based on the information obtained from the consensus sessions of experts (patients and professionals) and in accordance with the gamification methodology [39]. Although the final choice of the content will depend on the resulting decisions of the experts, it is intended to offer information and resources to the patient according to the level of HL identified and considering the main actions recommended to be incorporated to improve the overall health outcomes of these patients [12]. Thus, the participants in the experimental group will receive the mHealth app and will agree with the health care professional on 3 objectives related to the self-management of their disease, which they will have to achieve within a proposed period, being assisted by the mobile app, which will provide feedback and reinforcement in the achievement of these objectives. The stages and timing are described in Table 1. The intervention carried out in the control group participants will be based on usual clinical practice. Like the experimental group, they will agree with the health professional on 3 objectives they will have to achieve within the proposed time frame. This process (evaluation of the efficacy of the mHealth intervention with 2 groups) will last 12 months.

**Table 1 table1:** Stages of intervention.

Stage	Description	Timing (months)												
0	Detection of potential study participants. Presentation of the project and collection of informed consent.	✓^a^												
1	Baseline data collection for both groups.	✓												
2	For both groups, the patient and the practitioner will agree on the first health goal. On an individual basis, the nurse will present the main aspects related to the use and management of the app to the members of the expert group. The patient’s expectation of self-efficacy in using the app will be assessed to prevent adherence problems concerning the use of mobile health and difficulties in using the app (digital literacy) will be resolved.	✓	✓	✓										

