### Process

#### Assessment Eligibility

The health care professionals participating in the study will verify that the patient meets the eligibility criteria by consulting the digital history and interviewing the patient.

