**Characterization: clinical**				
	Main diagnosis	ICD-9-CM^a^ codes: 402.01 402.11 402.91 404.01 404.11 409.91 428.x	Registration	Medical history
	Years since diagnosis	0-100	Registration	Medical history
	Other secondary chronic pathologies	ICD-9-CM codes	Registration	Medical history
	HF^b^ signs/symptoms (dyspnea, orthopnea, fatigue, edema, oliguria, paroxysmal nocturnal dyspnea, high venous pressure, crackles R3/R4, murmurs and hepatomegaly)	Yes No	Registration or exploration or anamnesis	Medical history
	Cardiovascular risk factors (smoking, diabetes mellitus II, obesity [weight/BMI], hypertension, previous heart disease, dyslipidemia)	Yes No	Registration or exploration or anamnesis	Medical history
	HF functional classification (establishes the functional severity of HF based on stress tolerance)	I: No limitation. Regular physical activity does not cause dyspnea, fatigue, or palpitations. II: Slight limitation. Usual physical activity causes dyspnea, fatigue, or palpitations. III: Marked limitation (minor activities cause symptoms). IV: Inability to perform any activity. Symptoms even at rest.	NYHA^c^ Functional Classification [31]	Registration medical history

^a^ICD-9-CM: International Classification of Diseases, 9th revision, Clinical Modification.

^b^HF: heart failure.

^c^NYHA: New York Heart Association.

**Table 3 table3:** Measurement, recording, and data source of variables of main and secondary responses.

Type of variable		Register rank/format	Measurement	Source of data

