**Of main response**				
	Health literacy	0/50	HLS-EU-Q47^a^ [36]	Registration
		1-5/indicator	NOC^b^ code: 2015 [29]	Nursing record
	Self-management	1-5/indicator	NOC codes: 3102; 1803; 1830 [9,40]	Nursing record
		12-60	European Heart Failure Self-Care Behavior Scale [41]	Nursing record
	Number of readmissions 1m;12m	0-99	Registration	Registration medical history

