### Data Analysis: Data Encoding

A data matrix will be created, and data will be processed statistically using SPSS, version 22 (IBM). Statistical significance will be set at 95% (α=.05).

A uni-bivariate descriptive analysis will be performed to determine the sample distribution for each of the variables studied, both for the total sample and for each group. The characterization variables will be summarized using descriptive statistics, expressing qualitative variables in terms of frequency and percentages and quantitative variables in terms of mean and SD.

Before the analysis, the normality of the variables will be evaluated using the Kolmogorov-Smirnov and Shapiro-Wilk tests. Baseline differences in the variables related to the sample profile between the intervention and control groups will be compared using the Student *t* test when these are normally distributed and the nonparametric Mann-Whitney *U* test in case they are not. Differences between dichotomous qualitative variables will be established using the chi-square test or Fisher statistic when appropriate.

A contrast of means will be applied to test the efficacy of the intervention in terms of the normality distribution of the variables. The results will be analyzed using the nonparametric Wilcoxon signed-rank test, which will allow us to check if there are differences between 2 populations from 2 dependent or related samples, or the Student *t* test for normally distributed samples. For independent samples, the nonparametric Mann-Whitney *U* test will be used.

The strength of the relationship between continuous data will be determined from the Pearson or Spearman correlation. The intraclass correlation coefficient will be used if it is necessary to measure concordance between measurements at different times of the study. To identify sociodemographic and clinical characterization variables (independent variables) related to the intervention and the different response variables (dependent variables), multivariate, linear, logistic, or Cox proportional analyses will be performed, as appropriate for each response variable.

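### The stated analysis of readmissions does not use prior-year admissions, which are checked at entry; the cost is modest precision and no view of chance imbalance, not bias

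*Protocol article*

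**What the plan says.** **Entry.** Under Diagnostic Criteria, the second requirement is met by "Patients with at least one of the following complexity criteria". Six alternatives follow, the last being "2 or more hospital admissions in the previous 12 months". A patient can therefore qualify through repeated recent admissions, or through polypharmacy, social risk, pressure ulcers, malnutrition or tube feeding with few or no admissions.

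**Source.** Under Assessment Eligibility, professionals verify entry by "consulting the digital history and interviewing the patient".

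**Baseline variables.** The clinical part of Table 2 lists main diagnosis, "Years since diagnosis", other chronic diseases, heart failure signs, cardiovascular risk factors and NYHA class. It has no row for earlier admissions or for the complexity criterion met. Table 1 mentions "Baseline data collection for both groups" without itemising it.

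**Outcome.** Table 3 lists "Number of readmissions 1m;12m" under main response, as a count from 0 to 99. The Sample Size section sizes the trial on health literacy.

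**Analysis.** The Data Analysis section names t tests and rank tests for efficacy, including "For independent samples, the nonparametric Mann-Whitney" *U* test. Multivariable models are planned "To identify sociodemographic and clinical characterization variables (independent variables) related to the intervention and the different response variables".

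**Allocation.** Randomization is 1:1 within centre. No other balancing factor is named.

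**The concern.** The number of admissions in the year before entry is the same kind of quantity as the 12-month outcome, measured earlier. Among the items the article mentions, it is the natural candidate for the strongest baseline predictor of that outcome. The any-one-of-six entry rule makes it vary widely between participants, which is when adjusting for it helps most.

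The stated plan checks this history to decide entry and does not carry it further. It is absent from the printed baseline variables, from the efficacy tests and from the named source of model variables. Two things are at stake for the readmission comparison. Its confidence interval is wider than it need be. And if one arm happens to receive more frequently admitted patients, the baseline table as printed would not show it.

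**Working it through.** The article gives no readmission rate, dispersion or share of frequently admitted patients, so there is no figure of its own to reproduce here. The 118 per group concerns health literacy and serves below only as an arm size. The variance ratio does not depend on it.

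**Inputs**
- From the article: 118 per group; 30% loss, which would leave about 118 × 0.70 ≈ 83 if 118 is the number enrolled; 1:1 allocation.
- Assumed: share *p* with 2 or more prior-year admissions (0.3 to 0.5); yearly rates λ₀ without and λ₁ with that history; gamma-mixed Poisson counts with shape 2, so the variance within a subgroup is λ + λ²/2.

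**Formulas**
- Within-subgroup variance: W = (1−p)(λ₀ + λ₀²/2) + p(λ₁ + λ₁²/2)
- Between-subgroup variance: B = p(1−p)(λ₁ − λ₀)²
- Variance ratio, adjusted to unadjusted: W/(W+B)
- Unadjusted standard error of the difference in means: √(2(W+B)/118)
- Shift from a 10-point imbalance: 0.10 × (λ₁ − λ₀)

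| p | λ₀ / λ₁ | W | B | Ratio | Variance cut | SE cut | Unadjusted SE | Shift | Shift / SE |
|---|---|---|---|---|---|---|---|---|---|
| 0.4 | 0.5 / 1.5 | 1.425 | 0.240 | 0.86 | 14% | 7% | 0.168 | 0.10 | 0.6 |
| 0.5 | 0.4 / 1.2 | 1.200 | 0.160 | 0.88 | 12% | 6% | 0.152 | 0.08 | 0.5 |
| 0.3 | 0.5 / 2.0 | 1.638 | 0.473 | 0.78 | 22% | 12% | 0.189 | 0.15 | 0.8 |
| 0.4 | 0.4 / 0.8 | 0.736 | 0.038 | 0.95 | 5% | 3% | 0.115 | 0.04 | 0.3 |

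First row in full: W = 0.6 × 0.625 + 0.4 × 2.625 = 1.425; B = 0.24 × 1² = 0.24; ratio = 1.425/1.665 = 0.86; √0.856 = 0.925, a cut of about 7% in the standard error. Simulating 2,000 trials for each of the first three rows gave ratios of 0.87, 0.89 and 0.78, hence a range of about 11% to 22%.

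**Cross-check.** With correlation *r* between covariate and outcome, the residual variance is 1 − r²: 0.96, 0.91, 0.84 and 0.75 for r = 0.2, 0.3, 0.4 and 0.5. The table corresponds to r of about 0.2 to 0.5.

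**Chance imbalance.** The standard deviation of the between-arm difference in share is √(2p(1−p)/n). For p = 0.3 to 0.5 it is 6.0 to 6.5 percentage points at 118 per arm and 7.1 to 7.8 at 83. A 10-point imbalance at 118 per arm is thus about 1.5 to 1.7 standard deviations.

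These figures use the yes/no criterion and a linear adjustment of the difference in means. They carry over only approximately to the full count in a log-link model.

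**The case against.** The strongest reply is that this is a gap in a condensed article. The text introduces Tables 2 and 3 as a summary. Table 2 also omits other items checked at entry, such as the social-risk score and the cognitive screen, so it is plainly not a full record of what is collected. Covariate lists are often left to an analysis plan.

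Much of this stands, and it rules out three stronger readings that a reader might infer:

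- *The count is not recorded and could never be adjusted for.* Absence from a summary table does not show that. The models are not said to be restricted to the Table 2 variables, and pre-enrolment admissions can probably still be retrieved from the medical history, which is also the source for the outcome.
- *Readmissions lack a baseline value while the questionnaires have one.* Table 3 states no baseline time point for any measure.
- *The readmission comparison is biased.* Allocation is random within centre, so the unadjusted comparison is valid and its standard error already allows for chance imbalance.

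It is also fair that the trial is sized on health literacy, and that this comparison would be untouched.

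The reply does not remove the point. The article does more than stay silent: it names unadjusted efficacy tests and says where its model variables come from. Adjustment for the prior-year count is a clear improvement on that stated method. The PROFUND index in Table 3 does not fill the gap, because it is listed as a response and the article does not describe its content.

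**Conclusion.** The point holds as one of efficiency and transparency for a listed main response. As stated, the readmission analysis does not use its closest baseline predictor, although the information is seen at entry. The gain from using it is modest: about 11% to 22% of the variance (6% to 12% of the standard error) if rates are 3 to 4 times higher in frequently admitted patients, and about 5% of the variance at a twofold ratio. A 10-point imbalance would move the difference by 0.08 to 0.15 admissions per patient in the 3-to-4-fold scenarios, or 0.5 to 0.8 of a standard error, without being visible in the printed baseline table. Every rate, share and dispersion behind these figures is assumed. Validity is not in question, and the outcome is not the one that sized the trial.

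**What to change.** Add two items to Table 2, taken from the existing eligibility check: the number of hospital admissions in the 12 months before enrolment, and the complexity criterion or criteria met. Report both by arm in the baseline table. Pre-specify the prior-year count as a covariate in a count model for the between-arm comparison of readmissions, for example a negative binomial model with treatment arm and centre.

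The cost is small: the count and the criterion are noted from a record already opened at screening, and the model gains one term. The count should be fixed as of enrolment and obtained in the same way in both arms.
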